### Intervention

Following randomization to the treatment group (statin user) or the control group (statin non-user), clinical trial medication will be administered within four calendar days of symptom onset. Patients assigned to the statin user group will receive atorvastatin, either orally or via a nasogastric tube. A daily dose of atorvastatin 10 mg or higher was chosen to reflect clinical practice in Korea, where moderate- to high-intensity statin is commonly prescribed. A recent study from Korea [10] showed that most patients were prescribed moderate-to-high intensity statins (high intensity, 35%; moderate intensity, 65%; and low intensity, 5%), following the ACC/AHA 2013 Blood Cholesterol Management Guidelines [4] in acute CES patients. Subjects in the treatment group will take the clinical trial medication for 3 months, after which the continuation of statin therapy will be determined by their physicians in charge. In the control group, initiation of statin therapy will be at the discretion of the attending physicians after the initial 3-month period.

### Outcomes

The primary outcome is an occurrence of a major clinical event, defined as a composite of stroke recurrence, myocardial infarction, and all-cause death within 3 months of the index stroke. Secondary efficacy outcomes are (1) stroke recurrence, (2) all-cause death, (3) vascular death, and (4) major vascular events (comprising stroke recurrence, myocardial infarction, and vascular death). Secondary safety outcomes are (1) hemorrhagic stroke and (2) symptomatic hemorrhagic transformation.

In accordance with the predefined outcome capture protocol of the CRCS-K-NIH registry, a clinical research coordinator will prospectively collect outcome events during hospitalization and at the 3-month follow-up, either at patients’ routine clinic visits or through telephone interviews with the patients themselves or their caregivers. To ensure consistency in outcome capture during interviews, a set of uniform structured questionnaires will be utilized (Supplemental Table 2). Detailed definitions of each outcome are provided in Supplemental Table 3.

### Data and Safety Monitoring Board

The Data and Safety Monitoring Board (DSMB) of this trial is composed of four members (three stroke physicians and one independent biostatistician) who are not involved in the trial’s implementation. The primary objective of the DSMB is to periodically review safety data and determine whether the trial has reached a point where discontinuation may be warranted due to demonstrated efficacy or futility.

### Sample size estimates

To estimate event rates, a simulation study was performed using the CRCS-K-NIH registry database to closely reflect the characteristics of the trial’s target population. Data from a total of 5,261 patients who met the study’s selection criteria between April 2008 and November 2019 were extracted from the registry. During this period, the registry included 72,796 patients, of whom 65,801 had ischemic stroke, 63,340 presented within 7 days of symptom onset, 13,853 had cardioembolic stroke, 5579 did not receive statin therapy, and 5261 arrived at the hospital within 2 days of symptom onset.

The timing of randomization was based on a recent Korean study which showed that a significant number of major vascular events associated with statin therapy occur within the first month, particularly within the first 7 days [10]. To account for clinical feasibility, five randomization scenarios were developed (Supplemental Table 4), and scenario #3 was selected for simulation. Major event rates within 90 days between the treatment and control groups were compared for each of the 10 simulated datasets (Supplemental Table 5).

Considering that stroke severity is closely related to clinical outcomes, patients were categorized into three groups based on the National Institutes of Health Stroke Scale scores: mild (0–4), moderate (5–10), and severe (> 10). The estimated between-group differences in 90-day event rates were 2% for the mild group, 5% for the moderate group, and 25% for the severe group. These findings suggest that the overall 17% risk difference may have been driven disproportionately by the severe group, where indication bias and unmeasured confounders could have affected statin use and outcomes.

To minimize this potential bias, we based our sample size calculation on the moderate severity group. Using event rates of 7% in statin users and 12% in non-users (hazard ratio of 0.568), we estimated that 1036 patients and 99 events would provide 80% power to detect a 43.2% relative risk reduction at a two-sided alpha of 0.05, based on a group sequential log-rank test. An interim analysis at 50% of the information time is conducted using the O’Brian-Flemming type alpha spending function. Accounting for a 10% loss to follow-up, we plan to enroll 1152 patients under the intention-to-treat (ITT) principle.

### Statistical analysis

A log-rank test will be performed to test the primary hypothesis that statin users will have a lower incidence of major clinical events within 3 months compared to non-users. The same analysis will also be applied to assess secondary outcomes. Cox proportional hazard models will be used to adjust for any imbalances in baseline variables between the groups. The intention-to-treat (ITT) population is defined as all subjects who meet eligibility criteria and are hence randomized, while the per-protocol (PP) population consists of those who have more than 80% medication adherence and are assessed for the primary efficacy outcome among the ITT population. Subjects who take at least one medication after randomization will be classified as the safety population. While safety outcomes will be assessed using the safety population, both ITT and PP analyses will be performed for efficacy outcomes, but the results of the ITT analysis will be served as the primary determinant of trial outcomes.

We further define a non-RRCT population as individuals from the CRCS-K-NIH registry who meet trial eligibility criteria but choose not to participate. A comparison of baseline characteristics and outcomes between the RRCT ITT population and the non-RRCT population will be made to identify any significant imbalances in clinical characteristics between trial participants and nonparticipants.

An interim analysis will be performed at the time of 50 events, representing 50% of the expected primary efficacy endpoint events that have occurred. The purpose of the interim analysis is to calculate conditional power and make one of the following decisions: (1) declare efficacy and stop the trial early if strong evidence of efficacy in either study group is expected by the test statistic crossing the early termination efficacy boundaries, (2) continue the trial without any design changes if the conditional power is less than 50%, or (3) re-estimate the sample size and continue the trial if the interim result is promising, such as the conditional power being between 50 and 80% [14] All analyses except that of interim will be conducted using two-sided 5% level of significance. Details will be provided in the statistical analysis plan (SAP).

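### The safety population requires taking medication, which a no-placebo control arm managed as planned cannot do, so the definition conflicts with the two-arm safety comparison

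*Protocol article*

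**What the plan says.** All references are to the protocol article.

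- **Who is in the safety set (Statistical analysis).** "Subjects who take at least one medication after randomization will be classified as the safety population".
- **What it is used for (Statistical analysis).** "While safety outcomes will be assessed using the safety population, both ITT and PP analyses will be performed for efficacy outcomes". The safety set is thus the only population named for safety outcomes.
- **Which outcomes (Outcomes).** "Secondary safety outcomes are (1) hemorrhagic stroke and (2) symptomatic hemorrhagic transformation".
- **How secondary outcomes are tested (Statistical analysis).** After setting out a log-rank comparison of statin users with non-users for the primary hypothesis, the section adds: "The same analysis will also be applied to assess secondary outcomes".
- **Who takes study drug (Intervention).** "Patients assigned to the statin user group will receive atorvastatin, either orally or via a nasogastric tube", and "Subjects in the treatment group will take the clinical trial medication for 3 months".
- **What controls take (Intervention).** "In the control group, initiation of statin therapy will be at the discretion of the attending physicians after the initial 3-month period". The control group is labelled statin non-user, the trial is open-label, and no placebo or other control medication is described.

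**The concern.** A safety set defined by having taken at least one dose works in a placebo-controlled or active-controlled trial, where each arm has something to take. Here only one arm does. If the medication in the definition is the trial medication, a control who follows the plan for the full 3 months never meets the condition. The only controls who could meet it are those who took a statin off plan, and they are selected by something that happened after randomisation.

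At stake is the comparison of the two stated safety outcomes. Both hemorrhagic stroke and symptomatic hemorrhagic transformation can occur in a cardioembolic stroke patient who takes no statin, so a rate in the statin arm alone cannot separate a drug effect from background. The Study design section gives safety as an aim alongside efficacy, and that aim needs the non-user arm.

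**Working it through.** **Step 1. Arm sizes.** The document carries two totals. The Abstract presents 1036 as already allowing for 10% loss to follow-up. The Sample size estimates section derives 1036 and then inflates it to 1152. As background, the section's figures reproduce:

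- Hazard ratio: ln(1 − 0.07) / ln(1 − 0.12) = 0.568, as stated.
- Events by the Schoenfeld formula at hazard ratio 0.568, 80% power and two-sided 0.05: 99, as stated (power with 99 events is 0.803). This is a fixed-design formula without the small group-sequential adjustment.
- Patients: 99 / ((0.07 + 0.12) / 2) = 99 / 0.095 = 1042, within 1% of 1036.
- Inflation: 1036 / 0.90 = 1151.1, rounded up to 1152.

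The allocation ratio is 1:1 (Abstract), so each arm has 1152 / 2 = 576 or 1036 / 2 = 518 patients. The point does not depend on which total is right.

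**Step 2. Apply the definition to each arm.** Take medication to mean trial medication.

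- Statin arm: everyone who takes at least one dose of atorvastatin enters, so up to 576 (or 518).
- Control arm: no trial medication is assigned, and the plan mentions a statin for controls only after the 3-month outcome window. A control managed as planned does not enter.

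Result as written: about 576 versus 0, or 518 versus 0, apart from crossovers.

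**Step 3. Allow for crossovers.** The document gives no crossover rate, so the shares below are assumptions. Controls entering = control arm size × share who take a statin off plan.

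| Assumed share | Of 518 controls | Of 576 controls |
|---|---|---|
| 2% | 10.4, about 10 | 11.5, about 12 |
| 5% | 25.9, about 26 | 28.8, about 29 |
| 10% | 51.8, about 52 | 57.6, about 58 |

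These patients would be labelled controls but would all have taken a statin. They do not represent the non-user arm at any of these shares.

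**Step 4. Set the result against the rest of the section.** The two safety outcomes are classed as secondary outcomes, and secondary outcomes are to receive the users-versus-non-users log-rank test. That test needs non-users at risk. The population sentence removes them and the test sentence requires them, so the two cannot both be followed.

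**Step 5. Try the other reading.** If medication means any drug, nearly every patient hospitalised with acute stroke qualifies. Both arms stay in, but the condition then restricts almost nothing and does not define a safety set. The sentence needs changing on either reading.

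**The case against.** The strongest reply is that the text says medication, not trial medication, so the narrow reading is an inference. That is true, but it is the better inference. The preceding sentence defines the per-protocol population by medication adherence, and atorvastatin is the only study medication described. It is also true that the Intervention section opens by naming both groups before saying that trial medication will be administered. The sentences that follow give it to the statin arm only.

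A second reply is that the log-rank sentence and the safety aim show that a two-arm comparison is intended. This stands. A reader might infer that the investigators plan a single-arm tabulation, and the document does not support that. What it supports is a conflict between two sentences of the same section, of which the population sentence is the one that must change.

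A reader might also infer that the randomised safety comparison is lost altogether. That goes too far. The Outcomes section describes event capture in hospital and at 3 months without restriction by arm. Stroke recurrence and all-cause death are efficacy outcomes analysed by intention to treat, and the monitoring board's review of safety data is not tied to the safety population. The controls missing from the set are missing from an analysis, not from the data.

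Finally, the section defers details to a statistical analysis plan that is not shown. How to classify controls who start a statin early can properly be left there, and its absence here is no fault. The population definition is different: it is stated in the protocol and the outcomes are assigned to it, so an analysis plan that brought the controls back would contradict the protocol.

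**Conclusion.** The point holds as an error in a stated analysis set. On the natural reading, the safety population contains essentially no controls (about 576 versus 0 at 1152 enrolled, or 518 versus 0 at 1036), and the planned comparison of both safety outcomes cannot be made in the population named for it. This rests on three things: medication means trial medication, controls are managed as the Intervention section describes, and allocation is 1:1. The statin-arm counts are upper limits that assume everyone takes at least one dose. Crossovers would add some controls, but not a valid comparator.

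The scope is limited. The primary intention-to-treat efficacy result, which the plan makes the main determinant of the trial's outcome, is unaffected. Recruitment was still under way at the last status report (375 enrolled by 31 May 2025), so the definition can be corrected before the final analysis.

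**What to change.** Replace the safety population sentence. Remove the medication condition for controls, and state that hemorrhagic stroke and symptomatic hemorrhagic transformation are compared between arms, as randomised, in all randomised patients followed from randomisation. Add an as-treated set, made up of statin-arm patients with at least one dose plus all controls, as a sensitivity analysis.

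The order of the two matters. With the as-treated set as the main analysis, a statin-arm patient who bled or died between randomisation and the first dose would be dropped, while a control with the same event would be kept. That one-sided exclusion could favour the statin arm. The full randomised set avoids it.

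The cost is one or two sentences in the protocol, carried into the statistical analysis plan, with no new data and no change to the sample size. The downside is slight dilution. If a share d of the statin arm never takes a dose and has the same risk as controls, the observed risk difference shrinks by the factor (1 − d). The document gives no value for d; the loss is small if d is small, and the sensitivity analysis would show whether it matters.

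The per-protocol definition, which requires more than 80% medication adherence, raises the same difficulty for controls and could be reworded in the same edit.

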**Methods:**

This is a registry-based, multicenter, prospective, randomized, open-label, blinded endpoint (PROBE) study designed to evaluate the efficacy and safety of statin therapy in acute CES patients without established indications for statin use. Patients will be randomly assigned (1:1) to either statin users or non-users, with statin users receiving atorvastatin at a dose of 10 mg or higher throughout the study period. We plan to recruit 1036 participants to detect a relative risk reduction of 43% with 80% power and a two-sided alpha error of 0.05, accounting for a 10% loss to follow-up. The primary outcome is the occurrence of a major clinical event, defined as a composite of stroke recurrence, myocardial infarction, and all-cause mortality within 3 months after the index stroke. The secondary efficacy outcomes include (1) stroke recurrence, (2) all-cause mortality, (3) vascular death, and (4) major vascular events.

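### The final primary test is set at nominal two-sided 5%, which contradicts the O'Brien-Fleming-type spending function; the level should be about 0.049

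*Protocol article*

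**What the plan says.** Two sections of the protocol article bear on the level of the final primary test.

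- **Sample size estimates.** The planned size "would provide 80% power to detect a 43.2% relative risk reduction at a two-sided alpha of 0.05, based on a group sequential log-rank test". The same paragraph adds: "An interim analysis at 50% of the information time is conducted using the" O'Brien-Fleming type of alpha spending function (the article spells the name differently).
- **Statistical analysis.** "An interim analysis will be performed at the time of 50 events". At that look the trial may stop for efficacy, in favour of either group. It continues unchanged if conditional power is below 50%, and the sample size is re-estimated if conditional power is between 50 and 80%. The section then sets the level: "All analyses except that of interim will be conducted using two-sided 5% level of significance". It refers to the SAP for details.

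Neither section states a reduced level for the final primary test.

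**The concern.** Under a spending function, alpha used at an efficacy look is no longer available at the end. The final test must therefore use a level below 0.05. The level sentence in Statistical analysis excepts only the interim, so it places the final primary log-rank test at the full 5%. The two sections then give two different success criteria for the same test.

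The test in question is the ITT analysis of the primary outcome, which the article makes the primary determinant of the trial's result. A final p-value just under 0.05 would be positive under one section and negative under the other. That should be settled before any final data are seen.

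**Working it through.** **Inputs (protocol article).** Overall two-sided alpha 0.05, 80% power, 99 events, 1036 patients, event rates 7% and 12%, hazard ratio 0.568, one interim at 50% information (Sample size estimates); interim at 50 events (Statistical analysis); 1:1 allocation (Abstract, Methods). The information fraction is t = 0.50 as designed, or 50/99 = 0.505 at the stated trigger.

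**1. Reproduce the plan's figures.**
- Hazard ratio: ln(0.93)/ln(0.88) = 0.568. Agrees.
- Fixed-design Schoenfeld events: (1.960 + 0.842)² / (0.25 × (ln 0.568)²) = 98.13, so 99.
- Group sequential design with the boundary from step 2: 98.49, so 99. Agrees.
- Patients: the mean event rate is (0.07 + 0.12)/2 = 0.095. The group sequential design gives 98.49/0.095 = 1036.8 and the fixed design 98.13/0.095 = 1032.9. The stated 1036 fits the group sequential figure.

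The sample size therefore appears to assume the reduced final boundary already.

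**2. Boundaries under the named function.** I assume the Lan-DeMets form with 0.025 per side. The two-sided alpha spent at fraction t is 4 × [1 − Φ(2.2414/√t)]. The final critical value c₂ solves P(|Z₁| < c₁, |Z₂| < c₂) = 0.95 under the null hypothesis, with corr(Z₁, Z₂) = √t.

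| | t = 0.50 | t = 50/99 |
|---|---|---|
| Alpha spent at interim | 0.00305 | 0.00322 |
| Interim boundary, \|Z\| | 2.963 | 2.946 |
| Final boundary, \|Z\| | 1.969 | 1.969 |
| Final nominal two-sided p | 0.0490 | 0.0489 |

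**3. Type I error with a final test at 1.960, no re-estimation.** 1 − P(|Z₁| < c₁, |Z₂| < 1.960) = 0.0510 at either fraction. With other O'Brien-Fleming variants (the classical boundary, or the function applied to the two-sided 0.05 as a whole) it is 0.0520 to 0.0522.

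**4. Type I error with re-estimation.** The article gives neither the size nor the direction of the increase, so the scenarios are assumptions. The interim is at 50/99 events, conditional power is under the current trend, and the 50-80% zone triggers the increase.

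| Increase in events | Final at 1.960: benefit direction only | Final at 1.960: both directions | Final at 1.969: benefit direction only | Final at 1.969: both directions |
|---|---|---|---|---|
| 1.25-fold | 0.0506 | 0.0501 | 0.0496 | 0.0491 |
| 1.5-fold | 0.0502 | 0.0494 | 0.0492 | 0.0484 |
| 2-fold | 0.0497 | 0.0483 | 0.0487 | 0.0473 |
| To 80% conditional power, cap 1.5-fold | 0.0506 | 0.0501 | 0.0495 | 0.0491 |
| To 80% conditional power, cap 2-fold | 0.0505 | 0.0500 | 0.0495 | 0.0490 |

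At 1.960 the error straddles 5% (0.0483 to 0.0506). At 1.969 it stays below 5% in every scenario.

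**5. Power with the corrected boundary.** The drift is √(99/4) × |ln 0.568| = 2.814. With the 1.969 final boundary, power is 80.2%.

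**The case against.** **Wording, not design.** The group sequential specification in Sample size estimates already determines the final boundary. The 5% sentence could be meant as the overall level, or as the level for secondary, per-protocol, Cox and safety analyses. Step 1 makes loose wording the likely explanation. This stands as a view of intent. It does not remove the conflict, because the sentence excepts the interim alone and a reader applying it would test at p < 0.05.

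**Left to the SAP.** Exact boundary values commonly are. Here, however, the article states a level for the final test, and that level disagrees with its own design.

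**Re-estimation offsets the excess.** A reader might infer that the trial's overall type I error exceeds 5% as planned. The documents do not support this without qualification. The 5.1% applies to a trial without re-estimation. With it, the error can lie on either side of 5%, depending on rules that the article does not give. This objection stands against any unqualified claim of inflation. It does not rescue the 5% sentence, since the article does not present re-estimation as its means of controlling error.

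**Size.** The excess is about 0.1 percentage point, or about 0.2 under other O'Brien-Fleming variants. This also stands.

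**Conclusion.** The stated final level contradicts the named spending function. Under that function, with the interim at 50 of 99 events, the final primary test should be at a two-sided p of about 0.049, not 0.050. Without re-estimation the overall two-sided error is about 5.1%. With re-estimation it is slightly above or below 5%, and the documents do not allow a firmer statement. The trial's conclusion would differ only for a final p between about 0.049 and 0.050.

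The figures rest on the Lan-DeMets O'Brien-Fleming-type function at 0.025 per side, the usual normal approximation for the log-rank statistic, and an interim at the planned event count. The matter is minor in size but concerns the success criterion of the primary analysis, so it should be corrected before the final data are seen.

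**What to change.** Replace the level sentence in Statistical analysis with text to this effect:

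> The final primary log-rank test uses the boundary left by the O'Brien-Fleming-type spending function, given the alpha actually spent at the interim (nominal two-sided p of about 0.049 if the interim is at 50 of 99 events). This boundary is not relaxed if events are increased after re-estimation; the alpha spent at the interim remains as computed at the originally planned 99 events. The other, non-sequential analyses use the two-sided 5% level.

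The second sentence is needed because an increase changes the apparent information fraction. With 149 events (about 1.5-fold), 50/149 would imply only 0.0002 spent at the interim, whereas 0.0032 was in fact spent.

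The cost is a few lines of text. The 99 events, the 1036 patients and the 80% power are unchanged.
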